#### Stop criteria

The stop criteria have been agreed with the Trial Steering Committee (TSC) prior to starting recruitment. The internal pilot study will not proceed to full trial if: (1) the recruitment rate is substantially below target during the last 6 months of the internal pilot study and if the qualitative data suggests that we cannot improve recruitment by changing recruitment methods or (2) the qualitative data suggests that the interventions are not acceptable to participants.

### Outcomes and analyses of the full trial

#### Effectiveness of FITNET-NHS compared to Activity Management

The primary outcome will be disability at 6 months measured by the SF-36-PFS.

We will compare the mean SF-36-PFS scores at 6 months according to randomised allocation among participants with measured outcomes, using multivariable linear regression adjusting for baseline values of the outcome, baseline age and gender. Similar regression analyses will be conducted for secondary outcomes (linear regression for numerical outcomes and logistic regression for binary outcomes). For the primary outcome, we will conduct sensitivity analyses in which we also adjust for any prognostic variables for which there is a baseline imbalance between intervention arms. Further sensitivity analyses will use imputation for missing data (if appropriate). Three-month and 12-month outcome data will be analysed similarly. We will present summary statistics for the SF-36-PFS (at baseline, 3 months, 6 months and 12 months) for the participants allocated to FITNET-NHS who did and who did not complete at least module 19, as an initial investigation of the benefit of the intervention among those participants who were able to engage fully with it. We will conduct sensitivity analyses estimating the effectiveness of FITNET-NHS compared with Activity Management for the primary outcome only restricted to participants who fulfilled the CDC diagnostic criteria for CMS/ME at the time of recruitment to the trial.

#### Analyses of effectiveness for those with co-morbid mood disorders

We will estimate the effectiveness of FITNET-NHS compared with Activity Management on the primary outcome in participant subgroups defined by the presence or absence of baseline anxiety or depression, by using the age- and gender-specific clinical thresholds for each subscale on the RCADS. Evidence that the intervention effect differs between subgroups will be examined by adding interaction terms to the multivariable linear regression model for the primary outcome only.

#### Cost-effectiveness of FITNET-NHS and Activity Management

Our primary economic evaluation will compare differences in NHS costs and health outcomes, measured in Quality-adjusted Life Years (QALYs), between participants randomised to FITNET NHS and Activity Management in a cost-utility analysis.

NHS costs will include the costs of delivering each intervention (including future licence fee costs). We will record the number of video consultations in the Activity Management arm and the number of e-consultations in the FITNET-NHS arm. At each follow-up time point (3, 6 and 12 months) parents will be asked to complete an adapted resource-use questionnaire to measure the young person’s health service use (e.g. GP, specialist care or medications) as well as educational service (e.g. school counsellor) and family expenses in the last 3 months. We will also quantify the impact of the young person’s health on parental work using the WPAI:GH. In addition, Hospital Episode Statistics (HES) data and the Mental Health and Learning Disabilities Data Set (MHLDDS) from the Health and Social Care Information Centre (HSCIC) will be used to measure paediatric and CAMHS use in both arms. Resource use will be valued using national unit costs where available.

We intend to use the EQ-5D-Y to calculate QALYs. A valuation tariff for the EQ-5D-Y is being developed but is not yet available [41]. Some researchers have used the adult valuation tariff to estimate an index score for the EQ-5D-Y, although this may misrepresent young people’s values [42]. At the time of analysis, we will use the EQ-5D-Y valuation tariff, if available.

Depending on the prevalence of missing cost and outcome data, we may use simple or multiple imputation methods in our primary analysis. We will use a threshold willingness-to-pay of £20,000 per QALY [43] to estimate the incremental net monetary benefits of FITNET-NHS. We will use non-parametric bootstrapping methods to calculate 95% confidence intervals and create a cost-effectiveness acceptability curve to estimate the probability that FITNET-NHS is cost-effective at varying willingness-to-pay thresholds. Between-group analyses of incremental costs, QALYs and net benefits will be adjusted for age, gender and baseline EQ-5D-Y score.

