All data will be collected on REDCap and anonymised at source. Table-based authentication will be used which utilises the storage of username/password pairs in a database table. Participants will be sent a web link to REDCap which will only allow access to their data. All data will either be stored on secure University of Bristol servers and or in secure locked cabinets. They will create a password which they will use each time they log in. The schedule of data collection is shown in Fig. 2, the SPIRIT Figure [35]. An email will be sent to participants with a link to complete questionnaires online. If these are not completed, two automated reminders will be sent and then we will telephone participants where possible. If this is not successful, an email with a link to a reduced set of questionnaires will be sent out (SF-36-PFS, Chalder Fatigue Scale, school attendance, EQ-5D-Y and Clinical Global Impression Scale).

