### Sample size

Full trial: we plan to randomise 734 young people in the full trial. The study will proceed to full trial assuming the stop criteria (see below) are not met. Assuming 10% attrition (withdrawal or non-provision of primary outcome data) [16, 33], data on 660 young people will be available for the primary analysis. This gives 97% power at 1% significance to detect a 0.35-SD difference in treatment effect on the SF-36-PFS. The analysis of effectiveness in 198 young people with co-morbid mood disorders of anxiety and depression (30% of those recruited and with data available for analysis (after 10% attrition)) will have 80% power to detect a 0.4-SD difference at 5% significance. A difference of 10 points on the SF-36-PFS is considered to be the Minimal Clinically Important Difference (MCID) [36, 37]. The mean SF-36-PFS is 49.8 with SD 24.8 in young people with CFS/ME at assessment by the Bath specialist paediatric CFS/ME service (*n* = 1075). A 0.4-SD is 9.92 and, therefore, our trial is powered to detect the MCID of 10 in young people with co-morbid mood disorders of anxiety and depression.

We will perform sensitivity analyses on young people who fulfil the CDC diagnostic criteria. We estimate this will be 80% of those randomised (529 after 10% attrition) which will give us 98% power to detect a difference in treatment effect of 0.35 SD at 5% significance, which is at least the MCID.

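### The primary cost-utility analysis may use simple imputation; if the filled-in data are then bootstrapped, the intervals and acceptability curve will be too certain

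*Protocol article*

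**What the plan says.** All references are to the protocol article.

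- **Imputation.** The section *Cost-effectiveness of FITNET-NHS and Activity Management* makes the method conditional: "Depending on the prevalence of missing cost and outcome data", the authors write, "we may use simple or multiple imputation methods in our primary analysis". No level of missingness is attached to either method, and simple is not defined. Set against multiple, it most naturally means single imputation.
- **Uncertainty.** The same section continues: "We will use non-parametric bootstrapping methods to calculate 95% confidence intervals and create a cost-effectiveness acceptability curve". It does not say whether imputation comes before the bootstrap or is repeated within it.
- **Decision rule.** "We will use a threshold willingness-to-pay of £20,000 per QALY", from which incremental net monetary benefit is estimated.
- **Data sources.** At 3, 6 and 12 months "parents will be asked to complete an adapted resource-use questionnaire". Hospital and mental health datasets and counts of consultations add to this. The section on cost-effectiveness in co-morbid mood disorders adds linkage to general practice records for missing questionnaire data.
- **Non-responders.** Under *Outcome measures*, after failed reminders and telephone contact, "an email with a link to a reduced set of questionnaires will be sent out". The list for that set includes EQ-5D-Y but not the resource-use questionnaire.

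**The concern.** Single imputation puts one value in each gap and carries no record that the value was estimated. Resampling a dataset already completed this way does not bring that uncertainty back, because each resample draws imputed values as if they had been measured. The protocol permits this route for its primary economic analysis and names no step that would correct it.

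Two outputs would be affected: the 95% interval for incremental net monetary benefit, and the probability that FITNET-NHS is cost-effective at £20,000 per QALY. Cost-effectiveness is one of the trial's stated aims, so these outputs bear directly on its conclusions.

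**Working it through.** **1. The plan's own figures.** "we plan to randomise 734 young people in the full trial". With 10% attrition, 734 × 0.9 = 660.6, matching the stated 660. With 330 per arm, 0.35 SD and two-sided 1% significance (sidedness assumed), power is 97.3% against 97% stated. The clinical figures reproduce. The 10% refers to withdrawal or a missing primary clinical outcome; the article gives no rate for costs or QALYs. The missing fraction *m* below is therefore an assumption, shown over a range.

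**2. Arm-mean imputation, analytically.** Take *n* per arm, a fraction *m* missing completely at random in both arms, and each gap filled with its arm's observed mean.

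- The estimate equals the observed mean, so its true SE is SD/√((1−m)n).
- The completed data have variance (1−m)SD², so the reported SE is SD·√(1−m)/√n.
- Reported SE / true SE = √(1−m) × √(1−m) = 1−m. The difference between arms has the same ratio.
- Coverage of a nominal 95% interval = 2Φ(1.96(1−m)) − 1.
- A correct acceptability probability *p* is reported as Φ(z_p/(1−m)).

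| Missing (assumed) | SE ratio | Coverage | 0.70 reads | 0.90 reads |
|---|---|---|---|---|
| 5% | 0.95 | 93.7% | 0.710 | 0.911 |
| 10% | 0.90 | 92.2% | 0.720 | 0.923 |
| 20% | 0.80 | 88.3% | 0.744 | 0.945 |
| 30% | 0.70 | 83.0% | 0.773 | 0.966 |

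Numerical check at 10%, with unit SD and 734/2 = 367 per arm: true SE of the difference = √(2/(0.9 × 367)) = 0.0778; reported SE = √(2 × 0.9/367) = 0.0700; ratio 0.90.

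**3. Simulation of the bootstrap itself.** Inputs: 734 participants, 1:1, no true effect, normal outcome, data missing completely at random. Bootstrapping after arm-mean imputation (1,500 replicates) gave coverage of 90.3%, 86.7% and 81.9% at 10%, 20% and 30% missing. The Monte Carlo standard error is about 0.8 points at 10% missing, √(0.9 × 0.1/1500).

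**4. Other methods.** The inputs are the same, plus a baseline covariate correlated 0.5 with the outcome (800 replicates; 300 for the last row). For the two single-imputation rows, the model SE stands in for a bootstrap of the completed data.

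| Method | 10% | 20% | 30% |
|---|---|---|---|
| Single regression imputation | 92.1% | 87.5% | 82.1% |
| Single stochastic imputation | 91.4% | 90.7% | 84.8% |
| Multiple imputation, Rubin's rules | 94.8% | 95.4% | 94.9% |
| Regression imputation repeated in each bootstrap sample | 95.3% | 94.7% | 96.0% |

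The shortfall is not peculiar to mean imputation. It disappears with multiple imputation, and also when a simple method is repeated inside the bootstrap.

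**5. What the model leaves out.** It treats the whole outcome as missing for a fraction of participants. If only some cost components are missing, less of the variation in net benefit is imputed and the loss is smaller than shown.

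**The case against.** The strongest reply is that the plan does not commit to single imputation. The choice is tied to the amount of missing data, and the natural reading is graded: simple methods when little is missing, multiple imputation when more is. On that reading the 20% and 30% rows are where multiple imputation would be expected, and at 5% the shortfall is slight. This largely stands. However, with no cut-off stated, the reader cannot tell where the switch falls, and at 10% the loss is already about 3 points or more.

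Second, the order of imputation and bootstrap is not given, and the nested order is valid. This also stands, and it means that removing simple imputation altogether is not required. A condensed article may leave the sequence to a fuller plan. But the article itself puts simple imputation forward for the primary analysis, and its validity depends on that sequence.

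Third, a reader might infer that cost data are bound to be heavily incomplete, since they depend on parents and the reduced questionnaire set omits resource use. The article does not support that. It gives no rate, and it plans general practice linkage, Hospital Episode Statistics and mental health data, and consultation counts that do not rely on parental recall. The reduced set also retains EQ-5D-Y. These measures may limit missingness, though the linked records cannot supply an EQ-5D-Y score that was never completed.

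Finally, simple imputation is reasonable for an isolated item or a missing baseline EQ-5D-Y score used for adjustment. That stands and belongs in the fix.

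**Conclusion.** The point holds as a conditional one. The article permits a branch (single imputation of follow-up costs or EQ-5D-Y, followed by a bootstrap of the completed data) in which intervals are too narrow and the probability of cost-effectiveness lies too far from one half. It does not show that this branch will be taken, so the stronger statement that the economic intervals will be wrong is not supported.

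At an assumed 10% missing, coverage is about 90–92% and a correct probability of 0.90 would be reported as about 0.92, which is unlikely by itself to change a decision. At 20% the loss is larger: coverage is 88% under mean imputation. These sizes assume data missing completely at random, equal fractions by arm and whole outcomes imputed. The sample size, clinical power and SF-36-PFS analysis are unaffected.

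**What to change.** Amend the sentence on imputation in the economic section, and the health-economics analysis plan to match, before data are analysed:

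- Missing follow-up costs or EQ-5D-Y in the primary economic analysis are handled either by multiple imputation by arm combined with the bootstrap, or by imputation repeated within each bootstrap sample.
- Simple imputation is limited to baseline covariates or isolated items.
- A complete-case analysis is reported as a sensitivity analysis.

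The cost is a short text change, slightly more computing and, where data are missing, somewhat wider intervals than single imputation would report. No change to data collection or sample size is needed.

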### Randomisation

Participants will be randomised in a 1:1 ratio, by the research team, to receive either FITNET-NHS or Activity Management using an automated web randomisation service. Allocation will use minimisation to facilitate balance by age and gender, and preserve allocation concealment. Because of the nature of the intervention, it is not practical to blind either the participant, family or the clinical service to treatment allocation. GPs will be informed of the allocation.

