### Outcome measures

The following data will be collected from participants at the clinical assessment: age, sex, post code, ethnicity, symptoms (Centers for Disease Control and Prevention (CDC) and NICE criteria), months of illness, and diagnoses of co-morbid illnesses. At baseline participants will complete the following questionnaires: SF-36 physical function subscale (SF-36-PFS) [22], fatigue (using the Chalder Fatigue Scale and the Checklist Individual Strength (CIS) [23] fatigue severity subscale), school attendance, RCADS [21, 24], pain Visual Analogue Scale [25], EQ-5D-Y (EuroQoL health-related quality of life questionnaire, Youth version) [26] and the Clinical Global Impression Scale questionnaire [27], the Cognitive Behavioural Responses to Symptoms Questionnaire (CBRSQ) [28, 29] and the Children’s Negative Cognitive Error Questionnaire Revised (CNCEQ-R) [30]. Parents will complete the following questionnaires at baseline: an adapted existing Healthcare Resource Use questionnaire to measure health service use and the adapted six-item Work Productivity and Activity Impairment Questionnaire General Health V2.0 (WPAI:GH) [31].

The primary outcome is disability measured using the SF-36-PFS 6 months after randomisation.

Secondary outcomes will be measured at 3-, 6- and 12-month follow-ups unless otherwise stated: SF-36-PFS measured at 3 and 12 months after randomisation; fatigue (Chalder Fatigue Scale and CIS); school attendance; RCADS); pain Visual Analogue Scale; Clinical Global Impression Scale; EQ-5D-Y; parental completed: Healthcare Resource Use questionnaire; WPAI:GH. All these measures are important and relevant domains [32] that are used in UK services, Child and Adolescent Mental Health Services (CAMHS) and/or tested in previous trials [16, 33, 34].

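### Incremental costs and net benefits are not adjusted for baseline healthcare cost, although the baseline resource-use form is collected: a loss of precision, not a bias

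*Protocol article*

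**What the plan says.** The section on cost-effectiveness of FITNET-NHS and Activity Management names the adjustment covariates for all three economic quantities together: "Between-group analyses of incremental costs, QALYs and net benefits will be adjusted for age, gender and baseline EQ-5D-Y score". Baseline cost or resource use is not among them, and no other section adds it to the cost or net-benefit models.

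The Outcome measures section shows that the information is collected: "Parents will complete the following questionnaires at baseline: an adapted existing Healthcare Resource Use questionnaire to measure health service use". The cost-effectiveness section describes the use of the form after baseline only: "At each follow-up time point (3, 6 and 12 months) parents will be asked to complete an adapted resource-use questionnaire".

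Two other statements matter for comparison. The primary effectiveness model is fitted "using multivariable linear regression adjusting for baseline values of the outcome, baseline age and gender". The Randomisation section says: "Allocation will use minimisation to facilitate balance by age and gender"; prior healthcare use is not a minimisation factor.

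**The concern.** The covariate set treats the two halves of the economic comparison unequally. Baseline EQ-5D-Y is the natural baseline for QALYs, so the QALY difference is adjusted for where participants started. The cost difference has no matching covariate, although one can be built from data in hand. The clinical primary outcome, by contrast, is adjusted for its own baseline value.

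Healthcare costs are usually skewed, so a few heavy users can move an arm mean. If prior use predicts later use, part of that variation is predictable at baseline. Leaving it in the residual widens the interval for incremental cost. Any chance imbalance in prior use in the sample actually randomised also carries through to incremental cost, net benefit and the acceptability curve. Cost-effectiveness is one of the trial's stated aims, so these are not peripheral estimates. The design gives no direct protection, since allocation balances only age and gender.

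**Working it through.** **The plan's own figures.** The Sample size section states: "we plan to randomise 734 young people in the full trial". With 10% attrition, 734 × 0.9 = 660.6, and the plan uses 660, or 330 per arm. For a 0.35-SD difference at two-sided 1% significance:

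- SE of the difference = √(2/330) = 0.0778 SD
- Power = Φ(0.35/0.0778 − 2.576) = 0.973

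This agrees with the stated 97%. The plan states no precision or power for costs or net benefit, so nothing there can be reproduced, and this point changes none of the stated power figures.

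**Inputs for the check.**

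- Number analysed: 660, taken from the primary clinical analysis. The number with cost data may differ. The percentage change in SE does not depend on it.
- Allocation: "Participants will be randomised in a 1:1 ratio".
- r: the partial correlation of baseline with follow-up cost, given age, gender and baseline EQ-5D-Y, which are already in the model. The documents give no value and no cost SD, so r is assumed over 0.1 to 0.7.

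**Precision.** Adding the covariate multiplies the SE of incremental cost by √(1 − r²). The number that would give the same precision without the covariate is 660/(1 − r²).

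**Chance imbalance.** The SE of the between-arm difference in baseline cost is also √(2/330) = 0.0778 SD. An imbalance beyond 0.1 SD in either direction has probability 2 × [1 − Φ(0.1/0.0778)] ≈ 0.20, and beyond 0.15 SD about 0.05, ignoring any indirect balancing through minimisation. Without adjustment, a 0.1-SD imbalance moves the incremental cost by 0.1 × r SD, which is 0.1 × r/0.0778 standard errors.

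| Assumed r | √(1 − r²) | SE smaller by | Equivalent N | Shift from a 0.1-SD imbalance |
|---|---|---|---|---|
| 0.1 | 0.995 | 0.5% | 667 | 0.13 SE |
| 0.3 | 0.954 | 4.6% | 725 | 0.39 SE |
| 0.5 | 0.866 | 13.4% | 880 | 0.64 SE |
| 0.7 | 0.714 | 28.6% | 1294 | 0.90 SE |

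**Net benefit.** Net benefit is £20,000 × QALYs minus cost. In the simplest case baseline cost predicts only the cost part, and cost and QALY residuals are uncorrelated. If cost then makes up a share s of the residual variance of net benefit, the variance removed is s × r² rather than r². The gain is therefore smaller than in the table, but s cannot be obtained from the documents.

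**The case against.** The strongest reply is that the planned analysis is valid as it stands. Allocation is randomised, the covariates are named in advance, and the confidence interval already allows for chance imbalance. A reader might infer that incremental cost will be biased. The documents do not support that: the estimator is unbiased in expectation, and only precision and imbalance in the realised sample are at stake.

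A reader might also infer that the baseline questionnaire is never used. That goes too far. The questionnaire is listed among the secondary outcomes, and the effectiveness section plans similar regressions for secondary outcomes. Read together, these arguably provide a baseline-adjusted analysis of resource use, though they do not bring baseline cost into the cost or net-benefit models. Nor are costs wholly unadjusted, since baseline EQ-5D-Y, age and gender may predict some later use.

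The gain may also be small. Costs include delivering the interventions, which prior use need not predict. Participants enter after local assessment and investigation, so baseline use may partly reflect diagnostic work-up. Both could make r low, and at r = 0.1 the gain is negligible.

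Finally, follow-up use is drawn partly from routine hospital and mental-health data, so a questionnaire-based baseline cost is not like for like. That is true, but a covariate only has to predict the outcome; it need not be measured identically.

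These points limit the size of the benefit. None gives a reason to leave out a baseline value that is already collected.

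**Conclusion.** The point holds as a correctable weakness in a stated choice of covariates. The article names the set, so this is not a detail left to a later plan. The consequence is a less precise incremental cost and no correction for chance imbalance in prior healthcare use. The SE would be between 0.5% and 28.6% smaller for an assumed partial correlation of 0.1 to 0.7, with a smaller and uncomputable gain for net benefit. Confidence in the omission is high; confidence in its size is low, because no correlation or cost SD is given.

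One further inference should be resisted: that the article is deficient in not naming baseline cost as a predictor in an imputation model. It says only that imputation may be used, and that level of detail can be left to the full plan.

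**What to change.** Before any comparison of costs by arm, add baseline NHS cost to the covariates for the incremental cost and net-benefit models, keeping age, gender and baseline EQ-5D-Y. Build it from the NHS items of the baseline form ("an adapted existing Healthcare Resource Use questionnaire to measure health service use"), valued with the same unit costs as at follow-up. State that missing baseline cost will be filled by a simple imputation from baseline data, made without reference to arm or outcome, so that no participant is lost. The QALY model can stay as planned.

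No new data are needed. The costs are small: the baseline form has to be valued, and a skewed covariate may have high-leverage values, so influence should be checked. The result with the present covariate set can be reported alongside.
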